## Abstract

**Background:**

The prognosis of patients with cerebrovascular disorders is poor owing to their high residual rate of hemiplegia. Delayed withdrawal from synkinesis is a major cause of prolonged hemiplegia; however, effective rehabilitation has not been established. This single-arm, open-label study aims to evaluate the influence of a low-frequency treatment device on canceling synkinesis in patients with incomplete paralysis and cerebrovascular disorders.

**Methods:**

Eligible participants will include patients aged 20 years or older with incomplete paralysis, defined as upper limb Brunnstrom stage (BRS) of 2–4, who are within 1 month of onset of a cerebrovascular disorder. Qualified patients will be assigned to the novel rehabilitation treatment with IVES+ for 4 weeks. The primary endpoint of the study is the change from baseline in the upper-limb Fugl-Meyer Assessment (FMA) 2 weeks after the start of treatment. The secondary endpoints are changes in the amount of Functional Independence Measure, changes in the amount of upper-limb BRS, and changes in the amount of Barthel Index (BI) compared to the pre-intervention value at weeks 2 and 4; changes in the upper-limb FMA scores at 1, 3, and 4 weeks; changes in grip strength compared to the pre-intervention values at 1, 2, 3, and 4 weeks; and changes in upper-limb strength (manual muscle test) compared to the pre-intervention values at 1, 2, 3, and 4 weeks.

**Discussion:**

This study will explore the usefulness of IVES+ for recovery from motor paralysis in patients with cerebrovascular disorders.

**Trial registration:**

Japanese Clinical Registry, jRCTs052180226. Date of registration: February 1, 2022

## Key messages regarding feasibility

The protocol rehabilitation therapy in this study is a new method of handy portable low-frequency treatment device, integrated volitional control electrical stimulation (IVES+), that placed the stimulating electrodes in antagonistic muscles.The enrolment for the patients defined as upper limb Brunnstrom stage (BRS) of 2–4 is critical to evaluating the efficacy of this study.This study will explore the usefulness of IVES+ in recovery from motor paralysis to cancel synkinesis in patients with cerebrovascular disorders.The duration of hospitalization for rehabilitation is limited, and long-term efficacy is difficult to evaluate.

## Background

In cerebrovascular disease, which encompasses various clinical conditions with very different functional outcomes, one of the sequelae of motor impairment is residual hemiplegia [1]. Not all patients reach the end of the recovery process of cerebrovascular disorders from flaccidity to associative response to synergistic and then dissociative movements; recovery often ends in the middle, and functional impairment remains [2]. Clinical experience suggests that one of the major reasons for the high residual rate of hemiplegia and decreased activities of daily living (ADL) is the delayed withdrawal of synkinesis during the recovery from cerebrovascular accidents.

One of the characteristic outcomes of cerebrovascular disorders is the unintended activation of one limb when the homologous part of the opposite limb is active. Global synkinesis, also known as mirror movement, motor overflow, and contralateral irradiation, has long been documented [3]. Global synkinesis appears in multiple joints after the acquisition of muscle contractions when routine rehabilitation treatment is performed in patients with moderate hemiplegia caused by cerebrovascular accidents. After withdrawal from synkinesis, single-joint and isolated movements become possible, and recovery from motor paralysis progresses. In general, the potential improvement period of motor paralysis after a cerebrovascular accident is within 3 months [4], and early withdrawal from synkinesis in the acute phase is important for the recovery of motor paralysis. Brain images reveal that the presence of global synkinesis involves bilateral excitation of the motor cortex, such that one hemisphere reduces its inhibitory influence on the opposite hemisphere via transcallosal fibers [5, 6]. The elbow hypertonic position associated with post-stroke is typically present during elbow flexion, although forearm pronation appears to be more common [7]. Forearm pronation is performed by the biceps brachioradialis, brachialis muscles, and pronator teres.

The rehabilitation approach encourages practitioners to “make use of the remaining function,” that is, to “acquire activities of daily living by actively enhancing the function of the non-paralyzed side and compensating for the paralyzed limb [8].” However, with the development of neuroimaging of the central nervous system, the concept of neurorehabilitation has been proposed to promote the recovery of neural function after injury. Moving paralyzed muscles through the motor learning mechanism of the brain promotes cranial nerve reconstruction. Functional electrical stimulation (FES) is one approach to this neurorehabilitation [9]. The low-frequency treatment device, integrated volitional control electrical stimulation (IVES+) (OG Giken, Tokyo, Japan), is widely used to induce and enhance muscle contraction [10, 11]. IVES+ can be applied to small muscles, for which it is difficult to locate both the stimulation and recording electrodes [12]. However, the conventional application of this device for motor paralysis, which involves only direct stimulation, is not used for the purpose of canceling global synkinesis. We believe that a new method of FES in which stimulating electrodes are placed in antagonistic muscles can release global synkinesis. The protocol of this study was designed to assess global synkinesis inhibition.

## Methods

### Design

Reporting was in accordance with the checklist for pilot and feasibility trials [13]. This single-arm study was designed to explore the feasibility and clinical usefulness of a novel low-frequency device for canceling global synkinesis in patients with incomplete paralysis and cerebrovascular disorders (Fig. 1). In this study, Fugl-Meyer Assessment (FMA) will be used to evaluate the degree of synkinesis cancelation. FES has been used in conventional treatments to induce and enhance muscle contraction; however, in this study, FES will be used for patients with incomplete paralysis, defined as upper-limb Brunnstrom stages (BRS) 2–4, caused by a cerebrovascular accident. Eligible participants are patients aged ≥ 20 years with moderate hemiplegia caused by a cerebrovascular accident. The inclusion and exclusion criteria are listed in Table 1. Qualified patients will undergo a novel rehabilitation program using a low-frequency treatment device and regular rehabilitation for 4 weeks (Table 2).

**Fig. 1 Fig1:**
[figure not shown]
Study design. Twenty patients with incomplete paralysis and cerebrovascular disorders participated in this study. After confirmation of eligibility, the enrolled patients will be assigned to the study rehabilitation using IVES+. MMSE, Mini-Mental State Examination; BRS, Brunnstrom stage; FMA, Fugl-Meyer Assessment; FIM, Functional Independence Measure; BI, Barthel Index; MMT, manual muscle test, Adverse event; AE

**Table 1 Tab1:** Inclusion, exclusion, and discontinuation criteria

Inclusion criteria	
1. Within 1 month of a cerebrovascular event (cerebral infarction, cerebral hemorrhage, subarachnoid hemorrhage).	
2. With upper limb Brunnstrom stage (BRS) 2–4.	
3. Aged 20 years or older at the time of obtaining informed consent.	
4. Provides written informed consent to participate in this clinical study.	
Exclusion criteria	
1. Received treatments, such as botulinum therapy, repeated transcranial magnetic stimulation, and transcranial direct current stimulation, within 90 days of obtaining consent.	
2. With a history of surgery (including device therapy) or intravenous t-PA for a cerebrovascular event (cerebral infarction, cerebral hemorrhage, subarachnoid hemorrhage).	
3. Cognitive decline (Mini-Mental State Examination (MMSE) is 21 or less).	
4. Severe skin symptoms on the affected upper limb.	
5. Have a history of epileptic seizures.	
6. With a history of substance abuse or addiction (including alcoholism) at the time of enrolment and within the past year, or patients with complications.	
7. Using an implantable cardiac stimulator, such as a cardiac pacemaker or an implantable assisted heart.	
8. Using deep brain stimulation.	
9. With metal (excluding titanium products) implanted in the affected upper limb.	
10. Who are pregnant or may become pregnant. 11. Who are judged by doctors to be inappropriate as research subjects.	
Discontinuation criteria	
1. There was an offer to decline study participation or withdraw consent.	
2. Who were found not to meet eligibility after enrolment.	
3. The primary disease was completely cured and continued use was no longer necessary.	
4. The device therapy used in this study was judged unfavorable due to exacerbation of the primary disease.	
5. It is difficult to continue the study due to exacerbation of complications.	
6. It is difficult to continue the study due to illness.	
7. Although the frequency of use has been reduced according to the protocol, it is difficult to use even if the lower limit (less than 70% of the total planned number of uses) is reached.	
8. Who became pregnant.	
9. Poor compliance (if it is judged that less than 70% of the total planned number of uses will be used).	
10. Who cannot receive intervention due to hospital transfer.	
11. The entire study was discontinued	
12. For other reasons, the doctor judged it appropriate to discontinue the study.

**Table 2 Tab2:**
[figure not shown]
Overview of observation, clinical examination, and evaluation

*MMSE* Mini-Mental State Examination, *BRS* Brunnstrom stage, *FMA* Fugl-Meyer Assessment, *FIM* Functional Independence Measure, *BI* Barthel Index, *MMT* manual muscle test

This study will be carried out in compliance with the Declaration of Helsinki (revised in October 2013) and the Clinical Trial Act by the Ministry of Health, Labor, and Welfare in Japan. The investigator will provide sufficient explanation of the study to each patient and obtain written informed consent. The study protocol was approved by the Certified Review Board (Nara Medical University Certified Review Board: CRB5200002), and the research period is planned for February 1, 2022 to March 31, 2023. The organization of the study is shown in jRCTs052210163.

## Intervention

The major conventional method of using low-frequency treatment device for motor paralysis, which aims to induce and enhance the effect of muscle contraction, is the direct stimulation of the derived electrode and the stimulation electrode to the same muscle. In this study, we used IVES+, which can automatically change its stimulation intensity in direct proportion to changes in voluntarily generated electromyography (EMG) amplitude recorded with surface electrodes placed on the target muscle. In the novel FES, the derived electrode is placed on a muscle capable of voluntary contraction, and muscle activity is monitored. Next, a stimulation electrode is placed on the antagonistic muscle, which causes global synkinesis, and forced muscle contraction is promoted to perform motor control that decomposes global synkinesis (Fig. 2). FRAT application might cancel synkinesis and may help patients with cerebrovascular disorders withdraw from synkinesis at an earlier stage.

**Fig. 2 Fig2:**
[figure not shown]
Difference between conventional application and FRAT application of IVES+. The conventional application of this device for motor paralysis is only direct stimulation, in which the lead-out and stimulation electrodes are placed on the same muscle. In this FRAT study, a lead-out electrode was placed on a muscle capable of voluntary contraction, and its contraction was monitored. Subsequently, a stimulation electrode was placed on an antagonistic muscle against a muscle that causes synkinesis

The distinctiveness of this intervention is that it is not primarily intended for strengthening muscles. Instead, it is used to retrain the neuromuscular system to execute tasks that cannot be performed voluntarily. The patients will undergo the novel FES training 20 min a day for 5 days, for 4 weeks, for a total of approximately 20 sessions, and the number of repetitions will be determined based on individual participants’ strength and endurance. The number of standard rehabilitation sessions is, in principle, fixed for all subjects but varies depending on the condition.

### Endpoints

#### Primary endpoint

The primary endpoint is the mean and standard deviation (SD) for changes from baseline in the upper limb FMA at week 2. In addition, the effectiveness of this treatment will be examined by comparing the calculated mean value with 3.0, which is estimated as the amount of change in the case of conventional treatment. The FMA scale was developed as the first quantitative evaluative instrument for measuring sensorimotor stroke recovery in patients with hemiplegic stroke. The FMA is an efficient clinical examination method that has been widely tested in stroke populations. Its primary value is the 66-point motor domain, which has received the most extensive evaluation of upper-limb function [14]. The change in the FMA score can be used to evaluate the degree of cancelation of synkinesis. FMA has the advantage of being able to capture the patient’s overall picture and making it easier to predict the effects of rehabilitation [15, 16]. FMA has been reported to correlate with the degree of independence in activities of daily living [17]. In Japanese hospitals, the general length of stay in an acute care hospital is around 2 weeks; therefore, the timing of the endpoint was planned. We planned to conduct a subgroup analysis to adjust for the number of trials after this study.

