### Sample size

Since this is an exploratory study, the target number of cases is set at 20 from the feasibility viewpoint. At this time, if the average ± SD of the change amount of the main endpoint upper-limb FMA is estimated to be 6.0 ± 2.0, with reference to a previous report [22], the width of the 95% confidence interval of the change amount is approximately 1.9. As the amount of change in the case of normal treatment is expected to be 3.0 ± 1.0, it is considered that the effect of this treatment can be sufficiently confirmed.

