#### Statistical analysis plane

The primary endpoint is the change in the amount of upper-limb FMA from baseline to week 2. For efficacy evaluation, the full analysis set (FAS) and per-protocol set (PPS) will be used. The FAS is defined as the patient population excluded from the SS for any of the following reasons: ineligible cases after enrolment and cases with no data related to efficacy at any time after the start of study treatment. The PPS is defined as the patient population excluded from the FAS for any of the following reasons: violation of safety-related exclusion criteria, met criteria for study discontinuation, violation of effectiveness-related inclusion criteria, use of prohibited treatment, study rehabilitation compliance rate < 70%, or treatment period < 1 week.

Concerning the primary and secondary endpoints, the degree of improvement in parameters before and after intervention will be compared using the paired *t* test with a significance level of 0.05 and a tendency level of 0.10, and the improvement will be estimated using 95% CI. If the improvement in FMA between before and after the intervention is ≤ 0.10, we will proceed to the next pivotal clinical trial. Similarly, we will consider progression to the next trial if the BRS, FIM, grip strength, and BI values are ≤ 0.10. Missing values in the efficacy analysis will be supplemented with the immediately preceding value (last observation carried forward). We will analyze covariance with the intervention value as a covariate, and calculations will be performed using Statistical Package for the Social Sciences 22.0J (SPSS Japan, Tokyo, Japan).

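### The week-2 FMA change is to be compared with 3.0, but the planned interval and test are not tied to 3.0; the only stated test is against zero change

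*Protocol article*

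**What the plan says.** Three sections of the protocol article bear on how the primary endpoint is read.

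- **Primary endpoint.** "The primary endpoint is the mean and standard deviation (SD) for changes from baseline in the upper limb FMA at week 2". The next sentence adds that "the effectiveness of this treatment will be examined by comparing the calculated mean value with 3.0", a figure "which is estimated as the amount of change in the case of conventional treatment". The statistic compared is the mean. No test, interval or margin accompanies it.
- **Sample size.** "the target number of cases is set at 20 from the feasibility viewpoint". With the device, "the change amount of the main endpoint upper-limb FMA is estimated to be 6.0 ± 2.0", so that "the width of the 95% confidence interval of the change amount is approximately 1.9". The section then notes that "the amount of change in the case of normal treatment is expected to be 3.0 ± 1.0" and concludes that the effect can be adequately shown.
- **Statistical analysis plane (the article's heading).** Primary and secondary endpoints are compared before and after the intervention by paired t test, at 0.05 for significance and 0.10 for a tendency, and "the improvement will be estimated using 95% CI". Progression to a pivotal trial depends on the before-after FMA result being at most 0.10, read here as a p value. A covariance analysis is also mentioned. Nothing in this section refers to 3.0.

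**The concern.** The study has one arm, and patients enter within a month of the event, when recovery is expected anyway. The article puts that recovery at 3.0 points under normal treatment. The question about the device is therefore whether the mean change exceeds 3.0, not whether it exceeds zero.

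The article names the right reference value but gives the comparison with it no stated error control. The test and significance levels it does fix address zero change, which conventional care alone is expected to beat. Two misreadings are then open at reporting: a mean slightly above 3.0 taken as showing effectiveness, or a small before-after p value taken as showing benefit over conventional care.

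**Working it through.** **Inputs.** From the Sample size section: n = 20; change with the device 6.0, SD 2.0; change under normal treatment 3.0, SD 1.0. From the Statistical analysis section: levels 0.05 and 0.10, paired t test, 95% CI. SDs of 3, 4 and 6 below are assumptions to show sensitivity; they are not in the article.

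**1. The plan's own figure.** Full CI width = 2 × t(0.975; 19 df) × SD/√n = 2 × 2.093 × 2.0/√20 = 1.87. This reproduces the stated 1.9. Around a mean of 6.0 the interval is 6.0 ± 0.94, about 5.1 to 6.9, which is clear of 3.0. The Sample size section's conclusion thus makes sense only if the CI is held against 3.0.

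**2. Bare comparison of the mean with 3.0, device adds nothing.** The true mean is 3.0. With a symmetric sampling distribution, P(observed mean > 3.0) = 1 − Φ(0) = 50%, for any n and SD. In a simulation of changes scored in whole points (SD 1, 2 and 4), the probability is 46–49% for a mean strictly above 3.0 and 51–54% for a mean of at least 3.0.

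**3. The test that is written, device adds nothing.** For the paired t test against zero with true change 3.0, the noncentrality is 3.0/(SD/√20). At SD 2.0 this is 3.0/0.447 = 6.71. The probability of passing is above 99.9% at SD 1.0 and at SD 2.0, at either level. At the 0.10 level and assumed larger SDs it is 99.6% (SD 3), 94.4% (SD 4) and 69.5% (SD 6).

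**4. The planned CI read against 3.0.** Effectiveness would require mean − 2.093 × SD/√20 > 3.0.

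- False-positive rate at true mean 3.0: 2.5% (2.5–2.6% in the whole-point simulation).
- Mean needed at an observed SD of 2.0: 3.0 + 0.936 = 3.94.
- Power at true mean 6.0, noncentrality (6.0 − 3.0)/(SD/√20):

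| SD | Source | Power |
|---|---|---|
| 2.0 | plan | above 99.9% |
| 3 | assumed | 98.9% |
| 4 | assumed | 88.9% |
| 6 | assumed | 56.4% |

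**The case against.** The strongest reply is that the article never says a mean above 3.0 will be declared a success. It says only that the two figures will be compared, which may be descriptive. A reader might infer that the plan calls a useless device effective half the time. The text does not support that: the 50% belongs to one possible reading, and it is a property of any bare point-estimate rule.

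A reader might also infer that no interval is planned for this endpoint. That is wrong too. A 95% CI is planned, and the Sample size section sets its width beside 3.0, so a sympathetic reader could join the sections and hold the CI against 3.0.

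It can further be said that the manner of comparison is detail that an article leaves to the full protocol or SAP, that the study is exploratory with feasibility and safety named as its main objectives, and that the only decision with a stated consequence, progression, does not use 3.0.

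Much of this stands, and it lowers the seriousness of the point. It does not remove it. The article is not simply silent on the analysis: it fixes a reference value, a statistic, a test and error levels, and attaches the error levels to a different null. That progression rests on the zero-change test does not help, because that test is passed almost regardless of whether the device adds anything (step 3). An exploratory label does not settle how the comparison is to be read when the article says that effectiveness will be examined against 3.0 and that the sample is enough to show it.

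**Conclusion.** The point holds in a limited form. The comparison that bears on added benefit has no stated interval or test, the stated test and levels address zero change, and the planned CI is not linked to 3.0, although the sample-size reasoning depends on that link.

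The size depends on how the gap is filled. Read as a bare mean above 3.0, the comparison would favour a device that adds nothing in about half of trials. Read through the before-after test, such a device would show a positive result in more than 99.9% of trials at the article's own SDs. Read through the planned CI against 3.0, it would do so in 2.5%. The article does not commit itself to the first reading, so the 50% is conditional and not the plan's error rate.

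These figures assume 20 evaluable patients, an approximately normal mean, and 3.0 as a fixed, known value. Uncertainty in the 3.0 is not covered by any of them. For an exploratory study this is a clarification worth making before analysis, not a fatal fault.

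**What to change.** - **Primary endpoint:** state that the treatment is judged to exceed the conventional-care reference only if the lower limit of the planned two-sided 95% CI for the mean week-2 FMA change is above 3.0 (equivalently, a one-sample t test against 3.0 at two-sided 0.05, with the mean above 3.0). State that a mean above 3.0 with a CI that includes 3.0 is reported as inconclusive.
- **Sample size:** say that the CI width of about 1.9 is meant to be read against 3.0.
- **Statistical analysis:** say that the before-after test against zero describes change over time and is not evidence of benefit over conventional care. Reconcile this with the progression rule; editing the Primary endpoint section alone would leave the conflict in place.
- **Limitations:** state that 3.0 is treated as fixed and that its uncertainty is not covered.

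The cost is a few sentences. No new data or patients are needed, since the CI is already planned, and on the plan's own 6.0 ± 2.0 power remains above 99.9%. If the SD proves larger, the rule becomes more demanding: about 89% power at an assumed SD of 4.
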